### 2.6 The Nutrition Now resource

The Nutrition Now resource comprises four efficacious e-learning interventions (details including theoretical underpinning provided in **Additional File 1, Table S1**) offered through a website targeting different transitions early in life, from pregnancy to child age 2. The content and structure of the original interventions has been modified and adapted to context and user needs (**Figure 3**) in the relevant settings for this study (family-, MCH centre- and ECEC- settings). The modification also includes offering the Nutrition Now resource in English and Arabic languages in addition to the Norwegian version, as requested from both MCH and ECEC staff (on behalf of parents). Results from other adjustments in the development of the Nutrition Now resource will be described and published in detail elsewhere.

**Figure 3 f3:**
[figure not shown]
DIEM in the Nutrition Now project.

The Nutrition Now includes topics presented as core components addressing 1) the importance of diet early in life, 2) promotion of breastfeeding, 3), the importance of parental role in food provision and shaping child diet, 4) responsive feeding, 5) shared meals, 6) knowledge and experience of food preparation, 7) sensory play with vegetables, and 8) ECEC collaboration with parents (**Additional File 2, Table S2**). These topics are presented by videos, graphics, images and “easy to read” texts.

### 2.7 Project procedures in implementing the Nutrition Now resource

The process of implementing the Nutrition Now resource in the intervention municipality is guided by the Dynamic Integrated Evaluation Model (DIEM), the development of which was led by one of the co-authors ([name]) (54). We will use the iterative implementation process as proposed in DIEM, in which the planned implementation strategies can be adapted continuously based on collected data during the implementation process. The iterative process builds on employing rapid improvement cycles in a participatory approach that ensures a continuous process of changes. From a practice perspective, self-reflection and continuous development are important, and short, iterative interviews with stakeholders (ECEC and MCH) will serve as support for this (54). **Figure 3** shows elements from DIEM alongside the specific elements of the current study.

As shown in **Figure 3**, the tailored Nutrition Now resource is delivered through implementation strategies (2), already adjusted to needs and context (1) for use in the project’s iterative implementation phase. This enables further adjustments of the strategies as the project is rolled out and yields implementation outcomes continuously (3). Different implementation strategies target MCH staff, ECEC staff, the municipality level, and pregnant women and parents (**Figure 3**, **Tables 3**–**5**).

**Table 3 T3:** Implementation strategies targeting Nutrition Now implementation delivered through Municipality (Organizational level).

Category (55, 56)	Strategy (# denotes ERIC implementation strategy) (57)	The Actor *(deliver strategy)*	The Action *(specific action, steps or process)*	Action target *(affected by strategy)*	Implementation outcome(s)	Temporality and Dose	Justification
**Use evaluative and iterative strategies**	#4 Assess for readiness and identify barriers and facilitators	Implementation researchers	Meetings with stakeholders in municipality	Stakeholders in municipality	Adoption Appropriateness Feasibility	Pre-implementation from project start until the end of September 2022	Identify factors that may disrupt implementation, and strengths that can be exploited in the implementation effort
	#56 Purposefully reexamine the implementation	Implementation researchers	Conduct monthly short status meetings with public health coordinator	Public health coordinator	Feasibility	Monthly - during the pre-implementation and implementation process	Anchor implementation strategies, optimize implementation strategies to maximize intervention effectiveness
**Develop stakeholder interrelationships**	#6 Build a coalition	Implementation researchers	Conduct meetings with stakeholders	Stakeholders in municipality	Feasibility Fidelity	Pre implementation and during implementation	Ensure a good collaborative environment between stakeholders and research team at the municipality level
	#17 Conduct local consensus discussions	Implementation researchers	Conduct Mapping session	Stakeholders in municipality and politicians	Feasibility Sustainability	Pre-implementation, one time Amounts to 2 hours spent by each stakeholder/politician at municipality level	Establish a consensus for a need to improvement of early childhood nutrition in the municipality and the need for implementing Nutrition Now
	#47 Obtain formal commitments	University and municipality leaders	Written formal agreement between municipality and University	Municipality	Feasibility Sustainability	Pre implementation	Ensure key partners to commit to the signed agreement
**Engage consumers**	#Use mass media	Implementation researchers and stakeholders in municipality	Interviews in Newspapers, municipality website, blogpost	Target population in municipality	Adoption Reach	Pre implementation (newspaper interviews) and during implementation (website and blogpost)	Contribute to make Nutrition Now known and familiar to the target population
**Change infrastructure**	# Mandate change	Stakeholders in municipality	Declaration of priority given to Nutrition Now	MCH and ECEC in municipality	Adoption Fidelity Sustainability	Pre implementation and implementation - ongoing	Establish a determination to implement Nutrition Now

**Table 4 T4:** Implementation strategies targeting Nutrition Now implementation delivered through Maternal and Child Health (MCH) care center.

Category (55, 56)	Strategy (# denotes ERIC implementation strategy) (57)	The Actor *(deliver strategy)*	The Action *(specific action, steps, or process)*	Action target *(affected by strategy)*	Implementation outcome(s)	Temporality and Dose	Justification
**Use evaluative and iterative strategies**	#4 Assess for readiness and identify barriers and facilitators	Implementation researchers	Conduct in-depth interviews with 6 in 12 MCH nurses and one focus group discussion (FGD) with all 5 MCH midwives.	MCH nurse and midwives	Adoption Appropriateness Feasibility	Pre-implementation from project start until the end of September 2022 One in-depth interview and one FGD	Identify factors that may disrupt implementation, and strengths that can be exploited in the implementation effort
	#18 Conduct local needs assessment	Implementation researchers	Conduct in-depth interviews with 6 in 12 MCH nurses and one focus group discussion (FGD) with all 5 MCH midwives.	MCH nurse and midwives	Appropriateness Feasibility	Pre-implementation One in-depth interview and one FGD	Use the experiences and key knowledge the partners have regarding the target groups in order to tailor intervention to context
	#56 Purposefully reexamine the implementation	Implementation researcher	Conduct monthly short iterative interviews with one selected MCH nurse and midwife, respectively.	MCH nurse and midwives	Feasibility	During the implementation process (first six months) Six short interviews with staff	Optimize implementation strategies to maximize intervention effectiveness
**Adapt and tailor to context**	#51 Promote adaptability	Implementation researchers	Tailor the intervention to local context, e.g., by focusing on easy-to-understand texts, extensive use of visual and humorous elements as well as translating e-learning resource into English and Arabic language.	Pregnant women and parents of infants and toddlers	Acceptability Appropriateness Feasibility	Pre-implementation Dosage amounts to six months for 6 employees	Ensure that the Nutrition Now e-learning resource is suited/adapted for the target groups and context
	#63 Tailor strategies	Implementation researchers in collaboration with web designer	Develop ways to convey information about the e-learning resource considered as appropriate by MCH nurses and midwives, e.g., small information cards in three languages, posters at MCH center, instructional pamphlet targeting MCH staff.	Pregnant women and parents of infants and toddlers	Acceptability Appropriateness Feasibility	Ongoing during implementation Dosage amounts to one week of work	Tailor implementation strategies and leverage enablers identified.
**Develop stakeholder interrelationships**	#6 Build a coalition	Implementation researchers	Participate in internal educational meeting for MCH nurses. Arranged 3 + 3 workshops with MCH nurses and midwives, respectively.	MCH nurse and midwives	Acceptability Feasibility	Pre implementation until e-learning resource is distributed Amounts to 20 hours spent by MCH staff and 3 researchers	Ensure a good collaborative environment between stakeholders at the setting level
	#17 Conduct local consensus discussions	Implementation researchers	Conduct repeated workshops with MCH nurses and midwives separately (3 + 3) having discussions about e-learning resource suitability and content priorities.	MCH nurse and midwives	Appropriateness Feasibility	Pre-implementation Amounts to 20 hours spent by MCH staff and 3 researchers	Agree upon resource content deemed relevant for the target groups
	#38 Inform local opinion leaders	Implementation researchers	Conduct initial and repeated preparatory meetings with MCH service leaders.	MCH service leaders	Feasibility	Three meetings, in total 3 hours spent by staff and researchers	Anchor implementation strategies with service leaders to avoid misconceptions
**Train and educate stakeholders**	#15 Conduct educational meetings	Implementation researchers	Conduct educational meetings with MCH nurses, midwives and service leaders to teach them about the Nutrition Now innovation (the e-learning resource)	MCH nurse and midwives	Acceptability	Pre implementation and at the start of the implementation. Amounts to 1 hour spent by staff	Increase partners’ key knowledge about Nutrition Now resource content and project fundamentals
	#29 Develop educational materials	Implementation researchers in collaboration with web designer	Develop video and supporting written material to support staff: A short manual for MCH nurses and midwives briefly explaining how to convey the content and use of the e-learning resource to parents. Small information cards with QR codes leading parents directly to the e-learning resource. Educational videos explaining rationale and how to use the resource	MCH nurse and midwives Pregnant women and parents of infants and toddlers	Feasibility	Pre implementation phase 1. Post phase 1 to develop for phase 2. 3 days of work for two researchers and 2 days for web-designer	Need for instructional materials that make it easier for staff to convey the Nutrition Now resource and for pregnant women and parents to learn about how to use the resource
	#31 Distribute educational materials	Implementation researchers	Distribute educational material in person in connection with educational meetings	MCH nurse and midwives	Fidelity Feasibility	Pre-implementation. 2 days of work for 2 researchers	Provide educational materials to staff to facilitate delivering the intervention
**Support clinicians**	#58 Remind clinicians (including end-users of the e-learning resource)	Implementation researchers	Conduct follow-up meetings every six months Reminder e-mails with new resource content at regular intervals	MCH nurse and midwives Pregnant women and parents of infants and toddlers	Adoption Sustainability	Throughout implementation One day work for two researchers	Help MCH staff to recall information and/or prompt them to use the e-learning resource.

**Table 5 T5:** Implementation strategies targeting Nutrition Now implementation delivered through Early Childhood Education and Care (ECEC).

Category (55, 56)	Strategy (# denotes ERIC implementation strategy) (57)	The Actor *(deliver strategy)*	The Action *(specific action, steps or process)*	Action target *(affected by strategy)*	Implementation outcome(s)	Temporality and Dose	Justification
**Use evaluative and iterative strategies ** ** **	#4 Assess for readiness and identify barriers and facilitators	Implementation researchers	Conduct individual interviews with 12 ECEC staff and two focus group interviews Conducted meetings with ECEC heads	ECEC staff	Adoption Appropriateness Feasibility	Pre-implementation from project start until the end of September 2022 12 interviews and 2 focus group interviews	Identify factors that may disrupt implementation, and strengths that can be exploited in the implementation effort
** **	#18 Conduct local needs assessment	Implementation researchers	Conduct individual interviews with ECEC staff to assess needs	ECEC staff	Appropriateness Feasibility	Pre-implementation 12 individual interview and 2 focus group interviews	Use the experiences and key knowledge the ECEC staff have regarding the setting in order to tailor intervention to context
	#14 Conduct cyclical small tests of change	Implementation researcher	Conduct short iterative interviews with one selected champion at each ECEC unit	Champion at ECEC	Appropriateness Feasibility	During the implementation process (first six months) Every third week, 5-7 minutes each time	Optimize implementation strategies to maximize intervention effectiveness
	# 27 Develop and organize quality monitoring systems	Implementation researcher	Monitor implementation process through iterative interviews	Champion at ECEC	Adoption Feasability	During the implementation process (first six months) Every third week, 5-7 minutes each time	Use the input from champions to ensure quality and improvement of intervention strategies
	# 46 Obtain and use patients/consumers and family feedback	ECEC staff	Use advice in e-learning resource regarding parental collaboration and get feedback from parents	ECEC parents	Appropriatedness		Parental feedback to motivate further implementation by ECEC staff
**Provide interactive** **assistance**	# 33 Facilitation	Implementation researcher	Supportive researcher available for problem solving and support interpersonal relationship	ECEC Staff, ECEC champions	Feasability Fidelity	Ongoing during implementation	Ensure a positive collaborative environment between ECEC stakeholders at the setting level
**Adapt and tailor to context **	#63 Tailor strategies	Implementation researchers in collaboration with web designer	Develop ways to convey information about the e-learning resource considered appropriate by ECEC staff	ECEC staff	Acceptability Appropriateness Feasibility	Ongoing during implementation	Tailor implementation strategies and leverage enablers identified
**Develop stakeholder interrelationships **	#6 Build a coalition	Implementation researchers ECEC leaders Champion	ECEC leaders and champions participated in educational meeting ECEC leaders support champions, through e-mails and meetings Champions are encouraged to build relations with colleagues, through newsletters and the Nutrition Now resource	ECEC leaders and champions	Acceptability Feasibility	Pre implementation until e-learning resource is distributed Four meetings with ECEC leaders prior to implementation	Ensure a positive collaborative environment between ECEC stakeholders at the setting level
** **	#35 Identify and prepare champions	ECEC leaders and reseachers	Select a champion at each ECEC and clarify understanding of role as an implementation agent	Champion at ECEC	Adoption Acceptability Appropriateness Feasibility Fidelity	Pre implementation	Anchor and ensure the implementation at each ECEC unit
**Train and educate stakeholders **	#15 Conduct educational meetings	Implementation researchers	Conduct educational meetings with ECEC leaders prior to implementation about the importance of early childhood nutrition and seminars during implementation about how Nutrition Now is implemented in different ECECs	ECEC leaders and Champion	Acceptability Fidelity	Pre implementation and 2 seminars during the first 6 months of implementation. ECEC leaders: 4-5 hours spent by each, Champions: 1-2 hours	Increase partners’ key knowledge about Nutrition Now resource content and how it can be adopted
** **	#29 Develop educational materials	Implementation researchers in collaboration with web designer	Develop video and supporting written material (e-mails and messages within the e-learning resource) to support ECEC staff. Educational videos explaining rationale and how to use the resource. Posters to put up in the ECEC units	Champion and ECEC staff	Feasibility	Pre implementation	Need for instructional materials that make it easier for ECEC staff to convey the Nutrition Now resource and how to best use the resource
** **	#31 Distribute educational materials	Implementation researchers	Distribute educational material digitally and by mail	ECEC leaders and champion	Fidelity Feasibility	Pre implementation	Provide educational materials to staff to facilitate delivering the intervention
**Support clinicians **	#58 Remind clinicians	Implementation researchers	Reminder e-mails with new resource content at regular intervals and digital newsletters with support on how to progress with the intervention including change processes among ECEC staff	Champions at ECEC	Adoption Sustainability	During implementation	Help ECEC staff to recall information and/or prompt them to use the e-learning resource
**Engage consumers**	# 41 Involve patients/consumers and family members	ECEC leaders	Post URL to parent part of the e-learning resource on ECEC website	ECEC parents	Feasability Adoption	Start of the implementation, one time	Create synergy that enhance ECEC staff’s motivation to follow up the implementation
**Change Infrastructure**	# 44 Mandate change	ECEC champions	ECEC champion lead and holds meetings with ECEC staff regularly	ECEC staff	Adoption Feasability Sustainability	During implementation	Create structures (e.g., staff meetings) that enhance the implementation

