### 2.3 Study design

In this hybrid type 1 mixed methods implementation study we use a quasi-experimental design. The CONSORT Extension for pragmatic trials with its checklist was used (47). A single intervention municipality will be given access to the Nutrition Now resource and another control municipality (non-equivalent control) will continue as normal (**Figure 2**). Data from participants resident in the intervention municipality will be collected in the form of a pretest before they are given access to the Nutrition Now resource. Subsequently post-test data will be collected until the child reaches 2 years of age (See Data collection). Participants in the control municipality will be asked to provide pre- and post-test data but will not receive access to the Nutrition Now resource. Additionally, a time-series design will be used for comparisons within the intervention municipality between groups of participants exposed to the Nutrition Now resource at different levels of duration, and different types of exposure (See Data collection).

Enrolment started September 2022. The anticipated recruitment period is from September 2022-to April 2023, and we envision that the last participant (if recruited in early pregnancy in April 2023) will complete the study in September 2025. The ECECs were recruited prior to September 2022 and MCH personnel and parents will be recruited autumn 2022.

Intervention municipality provision of access to the Nutrition Now resource starts upon enrollment in the study and is expected to continue beyond the study period as long as the municipality finds it useful.

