### 2.5 Study participant groups and recruitment

The participant groups in this project are listed in **Figure 2**. All pregnant women and parents of 0-2-year-olds living in the intervention or control municipality are eligible for this study. For the sake of simplicity, we will refer to guardians/care givers/parents as parents although all are included in this notion. Further, all MCH nurses and midwives and ECEC leaders working in the intervention or control municipality, staff in ECECs in which the leaders have consented to participate, plus all other relevant municipality staff within public health in the intervention municipality are eligible to participate.

Pregnant women and parents of children aged 0-2 years will be recruited at 1) routine visits to the MCH centre by MCH nurses and midwives, 2) the municipality website and 3) the relevant ECEC’s website, with all routes leading to a registration website where participants are able to give digital consent. We have previously successfully recruited through MCH centres in a similar way (53). Persons from ethnic minority groups will be recruited for participation in in-depth-interviews, representing pregnant women, parents of 0–2-year-olds and parents of 1-2-year-olds in ECEC, *via* Non-Governmental Organizations and other arenas in the municipality using snowball sampling. ECEC leaders will consent on behalf of their ECEC and will then recruit team leaders at each unit and their staff by forwarding digital invitations to participate in the study. Midwives and public health nurses at the participating MCH centres and municipality stakeholders (public health workers, leaders) will be recruited by digital invitations from the research group.

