**Figure 4 f4:**
[figure not shown]
Overview of timeline for data collection, and exposure to the Nutrition Now resource (consisting of e-learning resources targeting different phases in a child’s 1000 first days) in the intervention municipality in the effectiveness trial. Pregnant women and parents of children between 0-2 years of age will be recruited from October 2022 until April 2023 through the MCH centre route. Participants will be exposed to age-appropriate content of the Nutrition Now resource and will be asked to respond to successive age-specific digital questionnaires depending on whether they are pregnant or the child’s age. Participants are given access to the Nutrition Now resource after completing the first questionnaire (pretest). ECEC staff will be recruited and complete the pretest questionnaire in September 2022, before getting access to the Nutrition Now-recourse. The post-test ECEC-staff questionnaire will be distributed seven months into the implementation of the intervention.

Consenting pregnant women (at any time during pregnancy), and parents of children between 0-2 years (at any time in this age interval) will first be asked to complete a short digital questionnaire to provide socio-demographic data in addition to expected due date (for pregnant women), or child’s age (for parents). Thereafter they will be asked to complete a second questionnaire tailored to the age of the child. Access to the Nutrition Now resource will be provided when the age-specific questionnaire is completed. The dose and duration of exposure to the Nutrition Now resource will differ between the participants depending on when they enter the study. Only those who are pregnant when entering the study between October 2022 and April 2023 will potentially be exposed to the whole range of intervention content, whereas a 1-year-old whose parent(s) enter the study in the same period, will be exposed to the “Toddlers 1-2 years” component and, if in ECEC, also the “Preschoolers 1+ years” component (**Figure 4**). Two-year-olds recruited at the regular health visit will be given access to the “Toddlers 1-2 years” component after completing the 24 months questionnaire.

ECEC leaders and staff will respond to questionnaires when consenting to participate in the study and seven months after getting access to the Nutrition Now resource.

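### QR cards and an ECEC-website link are described as taking parents to the resource with no registration or pretest step, which conflicts with the rule that access follows the pretest

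*Protocol article*

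**What the plan says.** **The access rule.** Section 2.3 says that data from intervention residents "will be collected in the form of a pretest before they are given access to the Nutrition Now resource", and that "provision of access to the Nutrition Now resource starts upon enrollment in the study". Section 2.8 is more specific: "Access to the Nutrition Now resource will be provided when the age-specific questionnaire is completed". The Figure 4 legend repeats that access comes after the pretest.

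**The links.** Section 2.7, Table 4, strategy #29 (educational materials) includes "Small information cards with QR codes leading parents directly to the e-learning resource". Table 5, strategy #41, gives ECEC leaders the action "Post URL to parent part of the e-learning resource on ECEC website". It is aimed at ECEC parents in general and timed as "Start of the implementation, one time". Neither row mentions registration, consent or a questionnaire. Information cards also appear in Table 4 under strategy #63, which continues throughout implementation.

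**Recruitment.** Section 2.5 names MCH visits, the municipality website and the ECEC website as recruitment routes, "with all routes leading to a registration website where participants are able to give digital consent". The Figure 4 legend puts recruitment of parents through the MCH centre between October 2022 and April 2023.

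**What relies on the rule.** Section 2.9.1 plans a comparison inside the intervention municipality with about 100 parent-child pairs that have had no exposure because of the way recruitment is arranged. It serves as a sensitivity analysis for residual confounding. Section 2.8 describes one group of this kind: two-year-olds recruited at the regular health visit, whose parents get access only after the 24-month questionnaire.

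**The concern.** The first age-specific questionnaire is a pretest only if the parent has not yet seen the content. Sections 2.3 and 2.8 guarantee this through the order of events, but two rows of the implementation tables describe routes to the content that skip that order. The routes run through the same MCH centre and ECEC websites that recruit parents, and over the same months. Table 2 puts 85% of 1-2-year-olds in the intervention municipality in ECEC, so a link on an ECEC website is within reach of most families with a child of that age.

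Two analyses would be at stake if the links are open:

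- Change from baseline in later entrants, meaning parents whose child is already eating solid food at the first questionnaire. Their baseline would contain part of the effect.
- The within-municipality comparison. The pairs treated as unexposed would include some that had used the parent content. The contrast would shrink, and its disagreement with the main comparison could be misread as residual confounding, which is what the comparison is meant to detect.

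**Working it through.** **Step 1: the passages side by side.**

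| Place | What it makes of access |
|---|---|
| 2.3 | Pretest first; access begins at enrolment |
| 2.8, text | Access on completing the age-specific questionnaire |
| Figure 4 legend | Access after the pretest |
| 2.5 | Recruitment routes lead to a registration site |
| Table 4, #29 | QR code leads directly to the resource |
| Table 5, #41 | Web link to the parent part, for ECEC parents, from the start of implementation |

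The first three rows require a step before access. The last two name the resource itself as the destination and give no such step. Section 2.5 names a different destination, the registration site, for recruitment routes. It does not say whether the QR code and the posted link are among those routes or are separate from them. No place says that the links open the content freely, and none says that they stop at a login.

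**Step 2: size of the dilution if the links are open.** Let Δ be the effect and p the share of parents who used the content before the first questionnaire. Assume, as the extreme case, that they already have the full effect.

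- Change from baseline: baseline mean = μ + pΔ, follow-up mean = μ + Δ, so the change due to the resource = Δ(1 − p).
- Within-municipality contrast: exposed mean = μ + Δ, mean of the pairs labelled unexposed = μ + pΔ, so the difference = Δ(1 − p).

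Section 2.5 gives Δ = 0.46 vegetable items per day from the earlier efficacy trial. The documents give no p, so a range is shown:

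- p = 10%: 0.46 × 0.90 = 0.414
- p = 20%: 0.46 × 0.80 = 0.368
- p = 30%: 0.46 × 0.70 = 0.322

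This is the largest dilution for each p. If earlier viewing gives only a fraction g of the effect, the contrast is Δ(1 − pg). With p = 20% and g = 0.5 it is 0.46 × 0.90 = 0.414.

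**Step 3: what that means for power, as illustration only.** Section 2.5 states that 100 fully exposed participants allow 0.5 items per day to be detected with alpha 0.05 and 80% power. No SD or comparator size is given there, so the figure cannot be reproduced directly. With two-sided alpha and 100 v 100, the implied SD is 0.5 / [(1.960 + 0.842) × √(2/100)] = 1.26. With power = Φ(0.5(1 − p) / (SD × √(2/100)) − 1.96):

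| SD (assumed) | p = 0 | 10% | 20% | 30% |
|---|---|---|---|---|
| 1.0 | 94% | 89% | 81% | 70% |
| 1.26 | 80% | 71% | 61% | 50% |
| 1.5 | 65% | 56% | 47% | 38% |

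These figures describe a comparison of 100 fully exposed pairs with about 100 pairs labelled unexposed, under the full-effect assumption of step 2.

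**The case against.** The strongest reply is that a QR code or link to a resource that sits behind registration would fit every passage. Section 2.5 already sends the ECEC website and MCH visits to registration, section 2.8 describes gated access, and a condensed article need not describe a login. Table 4 also shows the cards being developed and the educational material being given to staff. Nothing says that a parent receives a card before registering. This stands as a limit: early exposure is possible, not established. It does not remove the conflict, because the two table rows name the resource and not the registration site as the destination, and the ECEC link is posted for all ECEC parents while recruitment is open.

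A reader might infer more than the documents support in three places:

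- **The main comparison.** Section 2.9.1 compares families given all components with the control municipality. Under section 2.8 only those who enter during pregnancy can receive all components, so their first questionnaire holds no child-diet baseline to contaminate. Early viewing by an intervention parent is part of access under the treatment policy estimand. The factor (1 − p) does not apply here.
- **Leakage to control families.** The strategies concern the intervention municipality, and section 2.4 places the control municipality in another county. Nothing suggests that its families receive the cards or use those ECEC websites.
- **Adoption counts.** Table 1 takes adoption from recruitment data, as participants over those invited, so unregistered visitors would not enter it. Reach is defined as the number of users.

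**Conclusion.** The passages conflict on whether a parent can reach the content before registration and pretest, and they must be reconciled. The consequence is conditional. If the links open the content, change from baseline in later entrants and the sensitivity comparison with about 100 unexposed pairs are biased towards no effect. The contrast would be no lower than 0.41, 0.37 or 0.32 items per day for assumed pre-exposed shares of 10%, 20% or 30%, against 0.46. The share is an assumption, and the figures treat earlier viewing as giving the full effect, so real dilution at a given share would probably be smaller. The point goes beyond missing detail, because the unexposed status of those pairs, as far as the parent content is concerned, rests on the access rule. The documents do not support extending it to the main comparison, the control municipality or the adoption counts.

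**What to change.** - Have the QR code and the ECEC-website link open the registration page, with content released only after the first age-specific questionnaire, and word Tables 4 and 5 accordingly. If the links already work this way, say so in those rows.
- Add one item on prior use of Nutrition Now to the first questionnaire.
- Use the usage data that sections 2.8 and 2.9.2 already plan to collect to date each participant's first access, where the log can be linked to the participant. The prior-use item covers cases where it cannot.
- State that a questionnaire completed after first access counts neither as a pretest nor as an unexposed observation.

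The cost is one extra step for parents who follow a link and one extra questionnaire item. The usage data need no new collection.
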